# Effects of Combined Visual-Motor Response Training on Cognitive Function and Brain Plasticity Mechanisms in Various Populations: Protocol for a Single-Center, Open-Label, Controlled Clinical Trial

**DOI:** 10.2196/56424

**Published:** 2024-10-07

**Keywords:** visual-motor, response ability training, cognitive function, brain plasticity mechanism, study protocol

## Abstract

**Background:**

Cognitive impairment is one of the major diseases facing the aging population. The progressive decline of cognitive function can lead to declining health or even the loss of life, work, and social ability. Exercise and behavioral stimulation can increase neurotransmitters in the brain and improve overall health and cognitive function. Reactivity training can mobilize neuromuscular function and induce changes in brain plasticity, which may effectively improve cognitive dysfunction and delay the occurrence and development of Alzheimer disease; however, the evidence supporting its effectiveness is still limited.

**Objective:**

This study aims to explore the effectiveness and reliability of visual-motor reaction training in improving cognitive function, thereby promoting the application of novel nonpharmacological therapies.

**Methods:**

This study is a single-center, open-label, controlled clinical trial. A total of 78 participants will be recruited for the study, including an equal number of athletes, ordinary healthy college students, and ordinary older adults in the community. Participants will receive 2 weeks of visual-motor response training. The primary outcome of this study is to assess differences in functional magnetic resonance imaging (fMRI) at 2 weeks. The secondary outcomes were the following: acousto-optic response time, Hamilton Depression Rating Scale (HAM-D), Hamilton Anxiety Rating Scale (HAM-A), Mini Mental State Examination (MMSE), Activity of Daily Living (ADL) Scale, Subjective Cognitive Decline Questionnaire–9 (SCD-Q9), a 10-word memory test, and safety.

**Results:**

The study was approved by the Shanghai Clinical Research Ethics Committee on January 2, 2024 (SECCR/2023-162-01). As of September 11, 2024, we have completed the recruitment of all 3 groups of volunteers. We expect to complete data collection and analysis by February 2025.

**Conclusions:**

The purpose of this study is to compare improvements in brain perceptual motor functions and cognitive levels across different populations through response ability training and to explore the efficacy and safety of exercise-based nonpharmacological therapies in improving cognitive function. Other potential benefits include understanding the functional differences and perceptual characteristics of the brain’s perceptual-motor system between athletes and the general population and exploring the adaptability of the brain in acquiring skills during competitive sports training. This could provide an evidence base for early sports talent development and broader youth development.

**Trial Registration:**

Chinese Clinical Trial Registry ChiCTR2400079602; https://tinyurl.com/23fbbndw

**International Registered Report Identifier (IRRID):**

DERR1-10.2196/56424

## Introduction

Population aging has become an increasingly serious global problem. In recent years, the global older population has increased rapidly. It is estimated that by around 2050, the number of people aged 60 and older will reach 2 billion, accounting for more than 21% of the world’s population [1]. Older people have a high prevalence of cognitive impairment. China has the largest older population in the world, and cognitive impairment has a significant social impact on demographic imbalance [2]. Research shows that there are 15.07 million people with dementia aged 60 and older in China, including 9.83 million with Alzheimer disease, 3.92 million with vascular dementia, and 1.32 million with dementia [3]. With the accelerated aging of Chinese society, the increase of brain diseases, such as stroke, Parkinson disease, and Alzheimer disease, has increased cognitive dysfunction in the population; this seriously affects national health and greatly increases the economic and mental burden on patients, their family members, and society [4]. The demand for cognitive function training and cognitive impairment prevention in families and society is increasing daily, so the search for simple and easy-to-implement cognitive ability training methods is of great scientific significance and practical value.

Extensive studies on human beings have shown that exercise and response training are beneficial to overall health and cognitive function, especially in the aging population. In 1979, the United States Public Health Service detailed the role of exercise in health promotion, and for the first time, elevated national physical activity to the level of the national health plan, making exercise and health promotion a research hot spot. Exercise helps to improve the health of older people, enhances physical functioning, and reduces the incidence of chronic diseases and disabilities [5]. Studies have shown that exercise and behavioral stimulation can increase neurotransmitters in the brain, decrease levels of oxidative stress and inflammation, increase cerebral blood flow, and modulate the hypothalamic-pituitary-adrenal axis, which in turn alters the prefrontal cortex and the temporal lobe, increasing the volume of the hippocampal gyrus [6-8]. This change can promote neural activation in the cerebral cortex, enhance synaptic plasticity, and, it is hoped, improve cognitive ability and motor coordination [9].

In addition, response training is of great significance in ameliorating cognitive impairment and delaying the occurrence of dementia and Alzheimer disease [10]. People with different physical abilities may receive different results from reactivity training. Previous studies have found that the plasticity of the brain can change, particularly among professional athletes who have received extensive physical training [11-13]. In particular, volleyball players performed better in the implementation of control tasks and visual-spatial attention processing tasks. The action observation network plays an important role in these tasks, with the upper parietal lobe and auxiliary motor area being positively correlated with anticipatory capacity [14,15].

However, most forms of exercise are not suitable for the older population due to physical limitations. Therefore, the design and development of a combination of muscle and balance function training is an effective way to improve muscle coordination, prevent falls, and improve the cognitive state of older people. With advancements in technology, cognitive training equipment used in the community or by families is being widely used, which can better meet the issues of accessibility and portability of cognitive training. This study uses smart equipment to train the visual-motor response abilities of volleyball players, ordinary college students, and older people. We use functional magnetic resonance imaging (fMRI) to visualize the characteristic brain regions involved in perception of movement across different physical functions and explore the effects of cognitive training on cognitive function and the mechanisms of brain plasticity. The aims of this study are as follows: (1) to compare the functional advantages and characteristics of the brain perceptual-motor system in volleyball players and ordinary younger and older people; (2) to explore the influence of visual-motor response ability training on cognitive function in people with different physical functions; and (3) to preliminarily confirm the efficacy and safety of exercise-based nondrug therapy in improving cognitive function.

## Methods

### Study Design

This is a prospective, single-center, open-label, controlled clinical trial conducted between January 2022 and December 2025. This study will recruit professional volleyball players, ordinary college students, and older people without any professional sports training. In total, 78 participants will be recruited at the Shanghai University of Traditional Chinese Medicine, China, via the university website or posters, with 26 participants in each group. All participants will undergo baseline assessments, including acousto-optic response time tests and fMRI scans. This will be followed by 2 weeks of visual-motor response training. After 2 weeks, the outcomes of the intervention will be evaluated (Figure 1).

**Figure 1 figure1:**
[figure not shown]
Study flowchart. ADL: Activity of Daily Living; fMRI: functional magnetic resonance imaging; HAM-A: Hamilton Anxiety Rating Scale; HAM-D: Hamilton Depression Rating Scale; MMSE: Mini Mental State Examination; SCD-Q9: Subjective Cognitive Decline Questionnaire–9.

### Participants

The participants in the athlete group will be recruited from the high-level volleyball team of Shanghai. The college students will be recruited from the Shanghai University of Traditional Chinese Medicine through posters on campus and advertisements in campus media. Participants in the older population group will be recruited from healthy older adults in the community; in-person outreach will be conducted in randomly selected neighborhoods in Shanghai to attract active participants. Within each group, an equally spaced sampling method will be used to determine the final participants in the study. Participants need to understand and agree to this study, voluntarily undergo preintervention assessment and 2 weeks of visual-motor combination response training, and sign an informed consent form.

### Sample Size

Because of the exploratory nature of this study, it is impossible to estimate the total number of cases. Based on previous data, fMRI studies can be performed in groups of 12 participants with adequate statistical efficacy [16]. For the planned number of 20 participants in each group, if a 1-way ANOVA is used, it will be possible to detect a standardized mean-value effect (Cohen *d*) of 0.4, with a power of 80% and a significance level of 5% [17,18]. Assuming a loss to follow-up of 20%, the total sample size required for the study is 78 (n=26 in each group).

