### Statistical Analysis

All variables that can be measured directly will be analyzed descriptively by tabulating the empirical distributions. For continuous variables, mean (with SD), median, minimum, and maximum values will be documented. Classification variables will be recorded as incidence and percentage. Measurement data following a normal distribution will be analyzed with a 2-way repeated measures ANOVA. For intergroup factors, the participants will be divided into 3 groups, comprising athletes, young people, and older people. The intragroup factor will be evaluation time, which has 2 levels—before and after the intervention. The main effects and interactions among the 3 groups will be analyzed. For nonnormally distributed data, the Wilcoxon symbolic rank test will be used for intragroup analysis, and the Mann-Whitney *U* test will be used for intergroup comparison. The significance level of the statistical test is set at α=.05, and bilateral tests will be carried out. Differences in classification variables will be calculated using the *χ*^2^ test. *P*<.05 will be considered statistically significant.

The differences in brain fMRI images will be analyzed by MATLAB (R2014a; MathWorks) and Statistical Parametric Mapping (version 12; UCL Queen Square Institute of Neurology) [24]. Based on the intergroup analysis of the resting-state amplitude of low-frequency fluctuations (ALFF) and regional homogeneity (ReHo) indices, we will perform a flexible-design ANOVA to characterize the individual samples at each time point. Analyses will include time main effects, grouping main effects, time × grouping interactions, and statistical parameter diagrams. The post hoc test mask will reflect differences in brain regions where *P*<.01 and voxel >10, as determined by the ANOVA results. The intergroup analysis of functional connections will be done using GRETNA (Neuroimaging Tools and Resources Collaboratory) [25]. The functional connection differences among the 3 groups will be analyzed with a 2-factor repeated measurement ANOVA, and the intragroup analysis will be conducted with a paired 2-tailed *t* test. A *P* value <.01 is considered to show statistical significance. BrainNet Viewer (Neuroimaging Tools and Resources Collaboratory) will be used to draw schematic maps of brain regions with significant differences.

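### The stated 80% power for Cohen d = 0.4 with 20 per group is wrong: a three-group one-way ANOVA has about 18–23% power for that effect

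*Protocol article*

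**What the plan says.** The Sample Size section opens by calling the study exploratory and the number of cases impossible to estimate. It then gives a specific power statement. The design is "For the planned number of 20 participants in each group, if a 1-way ANOVA is used", and the claim is that "it will be possible to detect a standardized mean-value effect (Cohen *d*) of 0.4, with a power of 80"%, at a significance level of 5%. It goes on: "Assuming a loss to follow-up of 20%, the total sample size required for the study is 78 (n=26 in each group"). The Study Design section repeats the three equal groups, "with 26 participants in each group".

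The Statistical Analysis section plans a two-way repeated-measures ANOVA (group by time) for normally distributed measurements. For ALFF and ReHo it plans a flexible-design ANOVA with time, group and time × group effects, and a mask at P<.01 with more than 10 voxels. For functional connectivity it says "The functional connection differences among the 3 groups will be analyzed with a 2-factor repeated measurement ANOVA" and then "A *P* value <.01 is considered to show statistical significance".

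**The concern.** A one-way ANOVA with three groups is sized on Cohen f, the standard deviation of the group means divided by the within-group SD. Cohen d is a difference between two means in SD units. The two are not interchangeable: for three groups, f is well under half of the largest pairwise d. A claim of 80% power for d = 0.4 with 20 per group is therefore implausible on its face.

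This sentence is the protocol's only quantitative justification for its size. A reader will take it to mean that the trial can reliably find a between-group difference of 0.4 SD. If the group comparison is null, that reader could conclude that a 0.4 SD difference has been ruled out, when the test would miss such a difference about four times in five.

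**Working it through.** **Inputs, all from the Sample Size section:** k = 3 groups, n = 20 per group (N = 60), one-way ANOVA, effect 0.4 labelled Cohen d, alpha .05, claimed power 80%.

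**Method.** Exact noncentral F with df = 2 and 57 and noncentrality λ = N·f². The 5% critical value is 3.159.

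**Step 1: turn d into f.** Take d as the gap between the two extreme group means. The third mean then sets f:
- Third mean midway (smallest f): f = d/√6 = 0.4/2.449 = 0.163, so λ = 60 × 0.0267 = 1.60.
- Third mean equal to one extreme (largest f): f = d·√2/3 = 0.4 × 0.471 = 0.189, so λ = 60 × 0.0356 = 2.13.

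**Step 2: try to reproduce the plan's 80%.**

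| Reading of 0.4 | f | Power, 20 per group | Power, 26 per group | n per group for 80% |
|---|---|---|---|---|
| d, third mean midway | 0.163 | 18.0% | 22.5% | 122 |
| d, two means equal | 0.189 | 22.8% | 28.9% | 92 |
| f = d/2 (two-group conversion) | 0.200 | 25.2% | 32.1% | 82 |
| 0.4 is itself f | 0.400 | 77.6% | 88.3% | 22 |

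A two-sample t test of one pair of groups (d = 0.4, 20 per group, two-sided .05) gives 23.4%. No reading with d = 0.4 and the named test comes near 80%. The nearest is 0.4 as Cohen f (λ = 60 × 0.16 = 9.6), which falls 2.4 points short at 20 per group.

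**Step 3: what f = 0.4 means in SD units.** Reversing step 1, the spread between extreme means is 0.4 × 3/√2 = 0.85 SD to 0.4 × √6 = 0.98 SD.

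**Step 4: what 20 per group can detect.** Solving for 80% power at alpha .05 gives f = 0.41, a spread of 0.87 SD (0.4115 × 3/√2) to 1.01 SD (0.4115 × √6). With all 26 per group retained it is f = 0.36, or 0.76 to 0.88 SD.

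**Step 5: the same test at P<.01.** With 20 per group, 80% power needs f = 0.50, a spread of 1.06 to 1.23 SD, and f = 0.4 has 54.4% power. These are single-test figures. They ignore multiplicity across voxels or connections.

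**Dropout step.** 20/(1 − 0.20) = 25 per group, against 26 enrolled. This is slightly conservative and not at issue.

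**The case against.** The best defence is that this is a labelling slip. With 0.4 read as f, 26 enrolled less 20% loss leaves 20.8 per group, which gives about 79% power, so the enrolled size roughly delivers the intended 80%. That is probably how the figure arose, but the intended index is an inference. The sentence prints d and describes a standardized mean effect, and the two readings differ by more than a factor of two in SD units. The correction is still needed.

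A second defence is that the study is exploratory, the limitations are acknowledged and recruitment is complete. An exploratory study need not make a power claim, but this one does, and it calls 78 the required total. These points reduce the consequence without making the figure right.

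A third is that repeated measures could raise power. With a high pre–post correlation a time × group test can reach 80% for a small f: an assumed correlation of 0.7 with f = 0.163 gives 82%. The document gives no correlation and names a one-way ANOVA, so this does not rescue the statement.

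Three stronger readings are tempting, and the document does not support them:
- **That the sizing test contradicts the planned analysis.** The Sample Size section does not name the variable in the ANOVA. With two time points, a one-way ANOVA of pre–post change is equivalent to the group × time test, so no contradiction is established.
- **That the primary fMRI outcome is judged throughout at P<.01, so alpha .05 is wrong.** For ALFF and ReHo, P<.01 is a voxelwise mask threshold with an extent rule. It is a stated significance level only for functional connectivity, and the Outcome Measures section does not say which fMRI index is primary.
- **That the trial can detect only large effects.** This holds for between-group contrasts. The plan also lists a time main effect. Taking d = 0.4 as a standardized change (an assumption) with all 60 evaluable participants pooled, a paired test has about 86% power at .05.

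**Conclusion.** The power statement is wrong as printed. For d = 0.4 between extreme groups, 20 per group gives 18.0% to 22.8% power rather than 80%, and 80% would need 92 to 122 per group, some 4.6 to 6.1 times the planned 20. Treating 0.4 as Cohen f explains the figure but does not fully reproduce it: power is 77.6%, and 80% needs 22 per group.

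The result assumes three equal groups, a common within-group SD, a single outcome measure, and d taken as the largest gap among the three means. Using f = d/2 or a pairwise t test moves power only to 23–25%. The conclusion concerns between-group or group × time effects on one measure. It says nothing about the pooled time effect and does not give the power of a voxelwise or many-connection analysis.

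**What to change.** Leave the sample size as it is. Delete the claim about Cohen d of 0.4 and put in its place:

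> With 20 evaluable participants per group, a one-way ANOVA comparing the 3 groups on a single measure (for example, pre–post change) has 80% power at alpha .05 for Cohen f = 0.41, about 0.87–1.01 SD between the extreme group means. This refers to between-group (or group × time) effects and does not describe power for the time effect pooled over groups.

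Say which index the original calculation used. If a figure is also wanted at the P<.01 level set for functional connectivity, give f = 0.50 (1.06–1.23 SD) and state that it is a single-test figure that ignores multiplicity across voxels or connections.

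The cost is wording only, with no extra participants and no change of analysis. The stated detectable effect becomes less favourable.

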### Inclusion Criteria

The fulfillment of the following conditions is a prerequisite for all participants: (1) meet the “Technical Grade Standard of Volleyball Players” issued by the General Administration of Sports of China and obtain a grade II title or higher; (2) vision or corrected vision of 1.0; (3) no history of mental illness, brain trauma, and other diseases that affect brain structure and function; (4) meet fMRI scanning conditions, such as not having metal implants in the body or claustrophobia; and (5) being right-handed. Volleyball players should be aged 18 to 23 years; college students should be aged 18 to 23 years and have no professional sports training; older adults should be aged 55 to 70 years, have no professional sports training, and have a physical condition that meets the basic research needs (including self-care and normal movement of limbs and joints).

### Exclusion Criteria

Participants meeting any one of the following criteria will be excluded from this trial: (1) serious diseases of the heart and lung system; (2) diagnosis of mental illness, severe depression (suicidal tendency), or epilepsy; (3) metabolic systemic diseases, such as diabetes and uremia; (4) skeletal and muscle diseases, such as fractures, ligament injuries, severe arthritis, meniscus injuries, or spinal injuries; (5) hearing or visual impairment; and (6) use of drugs (eg, antiepileptic drugs, sedative drugs, and hypnotic drugs) that change the excitability of the cerebral cortex in the past 3 months.

### Dropout Criteria

Dropout criteria for patients are as follows: (1) withdrawal from the study and (2) incomplete implementation of the treatment plan.

### Suspension Criteria

If a patient develops other diseases or experiences serious adverse reactions during treatment, the trial will be discontinued by mutual decision of the participant and investigators.

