### Intervention

The implementation team of the intervention process includes a sports rehabilitation physician, a neurologist, a volleyball coach, a graduate student, and 2 undergraduate students. Before the formal intervention, the researchers were made familiar with the intervention equipment and intervention process through training. A between-group control design will be used with the same interventions. The 3 groups of participants will receive the same visual-motor response training for 30 minutes a day over 14 days. Response training will be completed with the help of gForceDual equipment and Neuro Rehab System (OYMotion). The participants download the Neuro Rehab System–based app and connect the gForceDual device to their mobile device through Bluetooth. During each training session, the gForceDual equipment will be secured to the transverse striation of the distal wrist of the participants’ right upper limb, and its electrode will be attached to the ventral part of the palmar longus muscle, brachioradialis muscle, radial carpal flexor muscle, and ulnar carpal flexor muscle. The response sensitivity will be adjusted via the app, and the participants will be guided by visual information to carry out wrist dorsal extension and flexion. The speed adjustment function in the app will be set to divide the training speed into gears, with a total of 10 gears. The default setting is sixth gear during the intervention. If an older person cannot keep up with the response, the app will downshift through gears; conversely, if an athlete can adapt well to a high gear, the app will upshift the gear. The researchers will record electromyographic signals produced by dorsal extension and flexion of the wrist.

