Adverse events are defined as any adverse experience that may be related to the trial treatment procedure that occurs during the course of the study. Any discomfort reported by the participants during the study will be carefully recorded.

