### Safety Measures

An excessively high gear or initial discomfort may cause dizziness, nausea, or fatigue in some participants during the audio-visual response training. During the training, research assistants will monitor the participants’ status and provide medical assistance as needed. If a participant is unable to adapt to our training model, the training session will be promptly terminated, and follow-up medical counseling and assistance will be offered.

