### Quality Control

All the researchers in this trial will receive a 5-day training course. Researchers involved in the treatment process will not be allowed to perform statistical analysis of the data. Data entry and statistical analysis will be the responsibility of professional researchers, and these participants will be unaware of the specific sources of data and the intervention process. The trial will establish an independent data monitoring committee, composed of 5 members, who will not participate in the operation of the trial and have no conflict of interest with the study. Members of the data monitoring committee will regularly review the research data to ensure the safety of participants and the reliability of the research data.

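### The suspension rule ties a safety stop to a joint decision with the participant, and no section shown lets the investigator alone end the remaining training

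*Protocol article*

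**What the plan says.** The rule stands in one sentence of the protocol article, under Suspension Criteria. Its triggers are a disease arising during treatment and a serious adverse reaction. Its consequence is that "the trial will be discontinued by mutual decision of the participant and investigators".

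Several other sections touch on stopping, leaving or safety:

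- Safety Measures expects that training "may cause dizziness, nausea, or fatigue in some participants during the audio-visual response training", has research assistants watch participants and arrange medical help, and adds: "If a participant is unable to adapt to our training model, the training session will be promptly terminated".
- Dropout Criteria lists "1) withdrawal from the study and (2) incomplete implementation of the treatment plan".
- Exclusion Criteria begins with "1) serious diseases of the heart and lung system; (2) diagnosis of mental illness, severe depression (suicidal tendency), or epilepsy" and goes on to metabolic, musculoskeletal and sensory conditions and certain drugs.
- Outcome Measures promises that "Any discomfort reported by the participants during the study will be carefully recorded".
- Quality Control says "Members of the data monitoring committee will regularly review the research data to ensure the safety of participants".
- Ethical Considerations lets participants leave whenever they wish.

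**The concern.** A decision to stop someone's training on safety grounds should be open to the investigator alone, just as a decision to leave should be open to the participant alone. The article secures the second and not the first. It names two parties for the stop and calls their decision mutual, in the situations where clinical judgement most needs to prevail.

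At stake is a narrow but real case. A participant has a serious reaction, or develops a disease that would have barred entry, and wishes to carry on. That participant could point to the sentence, and staff would have no express rule in this document to set against it. One of the three groups is aged 55 to 70, so a new illness during the course is not far-fetched, although the article gives no rate.

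**Working it through.** The article gives no figure on this point, so there is nothing to recompute. The check is a reading of every section that bears on exclusion, leaving, stopping, recording or safety review. There are seven.

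| Section | What triggers it | What it provides | Investigator alone may end the remaining course? |
|---|---|---|---|
| Exclusion Criteria | Listed conditions | Exclusion from the trial; no procedure for a condition that arises mid-course | Not stated |
| Dropout Criteria | Withdrawal; incomplete treatment | A classification; does not say who may initiate withdrawal | Not stated |
| Suspension Criteria | New disease; serious adverse reaction | Discontinuation by joint decision | No, on the natural reading |
| Outcome Measures (adverse events) | Any reported discomfort | Recording | Not stated |
| Safety Measures | Failure to adapt to the training | Prompt end of the session, with no agreement condition | Not stated; covers the session only |
| Quality Control | Regular review | Committee review of data | Not stated |
| Ethical Considerations | Participant's own choice | Participant may leave | Not applicable |

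None of the seven expressly lets the investigator alone end a participant's remaining training. One of the seven, Safety Measures, gives a stop with no agreement condition. This is a tally of text and does not measure harm.

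The reasoning then runs in four steps.

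1. A mutual decision of two named parties ordinarily means that both agree.
2. The participant never needs the investigators' agreement to stop, because Ethical Considerations already gives a one-sided exit. The word mutual therefore adds nothing on the participant's side and can bind only the investigator.
3. The session stop does not fill the space. It can be used at any session of the 14-day course, but its single trigger differs from the two in Suspension Criteria, and it ends a session, not the course.
4. Exclusion Criteria is most naturally an entry screen. If an excluding condition such as epilepsy or a fracture first appears during training, the rule that fits it is the one on new disease, which is again the joint decision.

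As to size, the intervention consists of participants being "guided by visual information to carry out wrist dorsal extension and flexion", for half an hour daily over 14 days. The effects the article anticipates are dizziness, nausea and fatigue. It gives no rate of serious reactions, so no expected harm can be calculated.

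**The case against.** The strongest reply is that the sentence is merely loose. Its verb is mandatory: discontinuation will happen. The phrase about a mutual decision may describe only how a required stop is agreed and communicated. The same sentence speaks of the trial where it must mean one person's participation, so a strict two-party rule may be more than it can bear. This stands in part. The agreement requirement is the natural reading and not explicit text. But if the stop were simply mandatory there would be nothing left to decide jointly, and the sentence does not say which element governs when the parties disagree.

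A second reply is that a condensed article need not set out investigator-initiated withdrawal, which the full protocol may contain. That is right as far as it goes: silence on this authority would be no finding. The point rests on what the article does state, namely who decides.

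A third reply is that the session stop would catch many serious reactions that occur during training, since such a person would usually be unable to go on. This also stands, and it narrows the gap. What remains is a new disease, or a reaction after which the person could still train and insists on doing so.

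Finally, recruitment was complete by September 11, 2024, with data collection and analysis expected by February 2025. An amendment may have had little training left to govern. The article does not say how much.

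A reader might also infer that the protocol forbids an investigator from stopping training, or gives the participant a veto. The text does not say so: it sets no express consent condition and does not state that training continues over the investigators' objection. Nor does it support a claim that a serious event would go unmonitored or unrecorded, since monitoring, recording and committee review are all provided.

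**Conclusion.** The point holds as a minor participant-safety correction to a stated rule. On its natural reading, the suspension sentence makes a safety stop of the remaining training depend on the participant's agreement, and no section shown gives the investigator that authority alone.

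This rests on two assumptions: that a mutual decision means agreement by both parties, and that the full protocol, which is not shown, does not state a different rule. If it does, the article's sentence should be brought into line with it.

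The practical consequence is small and cannot be quantified from the document. No estimate, test, sample size or adverse-event record is affected.

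**What to change.** Replace the sentence under Suspension Criteria with:

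> If a participant has a serious adverse reaction, or develops a condition listed in the exclusion criteria, the investigator will stop that participant's training; for any other new disease the investigator may stop it. Neither stop requires the participant's agreement, and the participant may withdraw at any time without the investigators' agreement.

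This keeps the stop mandatory for serious reactions and for conditions that would have barred entry. It leaves discretion only for other new illnesses, where a compulsory stop for something trivial would serve no one. It also makes clear that the individual's participation, and not the trial, is discontinued.

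The cost is one replacement passage in a protocol amendment. A participant stopped in this way already fits the existing dropout category of incomplete treatment, so analysis, sample size and recruitment need no change.
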